## Abstract

**Background:**

Acu-point specificity is a key issue in acupuncture. To date there has not been any satisfactory trial which can ratify the specific effect of acupuncture. This trial will evaluate the specific effect of BL33 for mild and moderate benign prostatic hyperplasia (BPH) on the basis of its effectiveness. The non-specific effect will be excluded and the therapeutic effect will be evaluated.

**Method:**

This is a double-blinded randomized controlled trial. 100 Patients will be randomly allocated into the treatment group (n = 50) and the control group (n = 50). The treatment group receives needling at BL33 and the control group receives needling at non-point. The needling depth, angle, direction, achievement of *De Qi *and parameters of electroacupuncture are exactly the same in both groups. The primary outcome measure is reduction of international prostate symptom score (IPSS) at the 6^th ^week and the secondary outcome measures are reduction of bladder residual urine, increase in maximum urinary flow rate at the 6^th ^week and reduction of IPSS at the 18^th ^week.

**Discussion:**

This trial will assess the specific therapeutic effect of electroacupuncture at BL33 for mild and moderate BPH.

**Trial registration:**

Protocol Registration System of Clinical Trials.gov NCT01218243

## 1. Background

For thousands of years, points of the fourteen meridians have always maintained their specific locations, and therapeutic indications. Point specificity is the central part of acupuncture and plays an important role in clinical practice. It has been proved by Cochrane reviews that acupuncture is effective for migraine prophylaxis, tension headache and chemotherapy-induced nausea or vomiting [1-3]. But there still remains a level of uncertainty about the specificity of some acupuncture ponits [4]. The difficulty in resolving this problem is due to the fact that acupuncture outcome is influenced by complex interplay of insertion depth, angle, and achievement of *De Qi*. Recently published trials in Germany show that acupuncture was no more effective than sham acupuncture for migraine, headache and knee osteoarthritis [5-8]. One could attribute it to adenosine's role in the mechanistic actions of acupuncture. According to the latest research [9], ATP release from keratinocytes in response to insertion and manual rotation of acupuncture needles results in an accumulation of adenosine that transiently reduces pain. If relief of pain is purely a response to mechanical stimulation, then it does not matter much which acupuncture point is being used. Hence, it is not appropriate to study point specificity with pain syndromes.

Study on point specificity began in China in the 1980s and it has been found that points of the fourteen meridians have specific functional regulatory effect on zang-fu organs [10-12], such as St36's specific effect for visceralgia and SI19's specific relationship with the ear. According to the results of those studies and our clinical practice, we took a trial showing that electroacupuncture at BL33 can reduce IPSS by 6.52 ± 0.41 (n = 47)[13] and 6.68 ± 2.84 (n = 87) [14]and improve the symptoms of difficult urination in mild or moderate patients with BPH. Its effect is better than that of terazosin. Also in our pilot trial (n = 40), 40 patients were randomized into the treatment group (BL33) and the control group (non-point acupuncture site located beside BL33). The result shows that electroacupuncture at BL33 has better effect in reducing IPSS and bladder residual urine and increasing maximum urinary flow rate than electroacupuncture at non-point. There is significant improvement with urinary frequency and nocturia in the treatment group as compared with the control group [15].

This trial is a large-scale prospective randomized trial after the pilot study. Patients and assessors are blinded with regard to acupuncture treatment given. It will compare needling at BL33 with needling at non- point. The same manipulating methods (needling depth, angle, direction and achievement of *De Qi,.*) could cause the same needle sensation between the two groups. As all points used in the trial are on the back area where patients are unable to see, thus blinding for the patients could be applied successfully. The study is registered with an identifier (NCT01218243) by Clinical Trials.gov in USA.

## 2. Methods and Design

### 2.1 Design

This study is a prospective randomized controlled trial and will be completed in Acupuncture Department of Guang'anmen Hospital affiliated to China Academy of Chinese Medical Sciences from Sep. 2010 to July 2012. Randomization is performed by Drug Clinical Trial Office affiliated to Guang'anmen Hospital. Computer-made opaque sealed envelopes are numbered consecutively. All of the envelopes are preserved by an investigator (who is uninvolved in acupuncture operation and data analysis). After the baseline assessment has been carried out and the informed consent has been obtained, an envelope is opened by the investigator according to patient's sequence entering the trial and the allocated treatment regimen is offered to the clinician. Two copies of the envelopes will be kept to guard against researchers trying to change the randomization.

Participants are recruited from PBH clinic in the hospital by the use of local newspaper advertisements and posted notices at clinic site. Patients on mediciation for urinary symptoms are requested to stop medication one week before baseline assessment. Before randomization, patients will complete 1-week baseline assessment which includes IPSS, bladder residual urine and maximum urinary flow rate and they will be divided into three groups according to their IPSS score, i.e. the mild group (0-7), moderate group (8-19) and the severe group (20-35). Patients belonging to the severe group will be excluded.

Enrolled patients will be randomized into the treatment group or the control group. The diagnosis and assessment will be made by an independent urologist who is uninvolved in the treatment process. Acupuncture will be given 5 sessions/week in the first two weeks and 3 sessions/week in the third and the fourth weeks, a total of 16 sessions.

The trial protocol is in accordance with the principles of the Declaration of Helsinki and has been approved by the review board and ethics committee of the hospital. Participants will be requested to sign an informed consent before any treatment is given. All patients have right to decide whether they would sign up or not and they can withdraw from the trial at any time (Figure 1).

**Figure 1 F1:**
[figure not shown]
**Flow chart of the trial**.

### Patients

According to our 40-case pilot trial and study of Christopher R. Chapple and Hong-Jeng Yu [16,17], to detect a reduction in IPSS of 7 with a two-sided 5% significance level and a power of 90%, 50 patients will be needed for treatment group and control group respectively (1:1 allocation) allowing for a 20% dropout rate [18].

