## Discussion

The point specificity has been a controversial research topic for a long time [20] and it has become a point of contention since the publication of those trials [5-8] in Germany as previously mentioned. But from the viewpoint of Nanna Goldman [9], anti-nociceptive effect of acupuncture is a general reaction to the mechanical stimulation leading to the belief that pain syndrome should not be used in point specificity study at the present time.

The reasons we choose BPH for point specificity include: 1) studies show that acupoints have specific effect in regulating function of zang-fu organs [10-12] and BPH is appropriate for this kind of study; 2) our previous study shows that electroacupuncture has effect in improving the symptoms of BPH and the effect is better than that of non-acupoint acupuncture; 3) a single point acupuncture is most suited for point specificity study.

In this trial, points used here are on the back area where patients unable to see and patients of the two groups have the same feeling because the manipulation methods are all the same. So patients are blinded as to which treatment they will receive. As the manipulation methods of the two groups are the same, the different effects between the two groups will be completely produced by point location, which will give a good explanation of point specificity. And also the placebo effect could be excluded and the specific effect of electroacupuncture at BL33 could be investigated. As electroacupuncture is also used in the control group with the same parameter and same insertion depth, part of treatment effect could be achieved. So part of specific effect of the treatment group will be excluded inevitably (Figure 3).

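### The 7-point IPSS reduction behind the 90% power claim is not a supported design difference for the between-arm primary test

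*Protocol article*

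**What the plan says.** - **Sample size** (protocol article, Patients): the trial is planned "to detect a reduction in IPSS of 7 with a two-sided 5% significance level and a power of 90" per cent. From this, "50 patients will be needed for treatment group and control group respectively (1:1 allocation", "allowing for a 20% dropout rate". The basis is given as the 40-case pilot and two cited studies. The 7 is not labelled as a difference between arms, and no SD is printed.
- **Primary outcome** (Outcome measures): reduction in IPSS at week 6 relative to baseline, so the word *reduction* there means a change within a patient.
- **Primary test** (Statistical analysis): analysis of covariance, asking whether BL33 is more effective than the non-acupoint site. This is a comparison between arms.
- **Earlier response to BL33** (1. Background): "electroacupuncture at BL33 can reduce IPSS by 6.52 ± 0.41 (n = 47)[13] and 6.68 ± 2.84 (n = 87". Neither figure after the ± is labelled SD or standard error.
- **Expected control response** (Discussion): "As electroacupuncture is also used in the control group with the same parameter and same insertion depth, part of treatment effect could be achieved".
- **Pilot** (1. Background): 40 patients randomized to BL33 or to a non-point beside it, the same contrast as in this trial. Its between-arm difference and SD are not given.

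**The concern.** A power statement has to refer to the contrast being tested. Here that is the difference between two needling sites under the same stimulation, with a control that the article itself expects to be partly effective. The figure given is a reduction of 7, about the size of the total improvement seen with BL33 before. The difference between sites should be smaller than that total.

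The trial's purpose is to decide whether point location matters. If it ends without a significant difference, a reader will take the 90% at face value and may treat the result as strong evidence against point specificity. If it ends with a significant difference of one or two points, that result may be set against a planned 7 that never described the comparison. In both cases the protocol does not say what size of site effect the trial was designed to find.

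**Working it through.** **Inputs.** Two-sided 5%, 90% power, 7 points, 50 per arm, 20% dropout (Patients). Evaluable per arm: 50 × (1 − 0.20) = 40. SD 2.84 (1. Background, n = 87, taken as the SD of change). If the 0.41 of the n = 47 study is a standard error, its SD is 0.41 × √47 = 2.81, which agrees.

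**Step 1: can the plan's 50 per arm be reproduced from a between-arm 7?**
n per arm = 2 × [SD × (1.960 + 1.2816) / 7]²
- SD 2.84: 2 × (2.84 × 3.2416 / 7)² = 3.5, so 4 per arm by the normal formula; 5 by the t-test (power 92.5% at 5 per arm). The plan states 50.
- Larger assumed SDs, normal formula: 11 per arm at SD 5, 16 at SD 6, 22 at SD 7. After 20% dropout these become 14, 20 and 28.

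**Step 2: what SD would give 50 per arm?**
SD = 7 × √(40/2) / 3.2416 = 9.66 (normal). By the t-test the standardized difference at 40 per arm is 0.734, so SD = 7 / 0.734 = 9.54. Against 2.84 the ratio is 9.66 / 2.84 = 3.4. Other conventions do not bring it down: 10.7 for a one-sided test, 10.8 with no dropout allowance.

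**Step 3: is a between-arm 7 compatible with the article's own data?**
Required control change = BL33 reduction − 7. With 6.68 this is −0.32, with 6.52 it is −0.48: at the earlier mean responses the control arm would have to worsen slightly. The Discussion expects it to improve.

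**Step 4: is the 7 a change from baseline instead?**
Then it is not the tested contrast. It does not give 50 per arm either: a one-sample calculation at SD 2.84 needs 2 patients, and 40 patients would correspond to an SD of 7 × √40 / 3.2416 = 13.7.

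**Step 5: what 40 evaluable per arm can detect between arms.**
Detectable difference at 90% power = 0.734 × SD (t-test).

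| SD of change | Detectable difference | Power for a 2-point difference |
|---|---|---|
| 2.84 (article, taken as SD) | 2.1 | 88% |
| 4 (assumed) | 2.9 | 61% |
| 5 (assumed) | 3.7 | 43% |

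The power column uses the normal formula. The 2-point difference is an illustration; the article gives no between-arm difference.

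**The case against.** The strongest reply is that the calculation's inputs are not in view. The Patients section draws on the pilot and two cited studies, whereas the 2.84 comes from a different study in the Background. An unprinted SD near 9.7 would reproduce 50 per arm. The 7 may also be the expected BL33 response, with a control value used in the calculation but left out of the article. At SD 2.84, for example, 7 against about 4.9 (7 − 2.1) would give 90% power at 40 evaluable per arm and would fit a partly effective control. Nor is 7 far from the earlier data: taking 2.84 as an SD, the 95% interval for 6.68 is 6.68 ± 1.96 × 2.84 / √87, about 6.1 to 7.3.

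Most of this stands as a limit on the conclusion. An article may omit the SD, and that omission is not the point. It does not rescue the sentence as written. A BL33-arm response of 7, even if accurate, is not the difference the trial tests. A between-arm 7 conflicts with the Background and the Discussion whatever SD was used.

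Three stronger readings should be set aside.
- A reader might infer that 7 can only be a within-arm change. That is a reasonable inference from how *reduction* is used under Outcome measures, but the Patients section does not label it.
- A reader might call an SD of 9.5 to 9.7 impossible, because eligible baseline scores run from 0 to 19 and so cannot have an SD above 9.5. That ceiling applies to baseline scores. It does not bound the SD of change, since the week-6 score is not capped at 19.
- A reader might conclude that the trial is underpowered. The documents give neither the expected site difference nor the SD needed to say so.

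**Conclusion.** The point holds on either reading of the 7. As a change from baseline, it leaves the primary between-arm test with no stated power. As a between-arm difference, it is larger than the whole earlier BL33 reduction and needs an SD about 3.4 times the one in the article, at which about 5 evaluable per arm would be enough instead of 40.

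This rests on taking 2.84 as an SD of change and on the 20% dropout leaving 40 per arm. It shows that the design difference is mis-stated and unsupported by the article's own figures. It does not show that 100 patients are too few: 40 evaluable per arm gives 90% power for about 2.1 points if the SD is 2.84, but only for larger differences if the SD is 4 or 5. Which case applies cannot be settled from the article.

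**What to change.** Replace the 7-point figure in the Patients section with the expected between-arm difference in 6-week IPSS change, its SD and the source of both. The sponsor's randomized 40-patient pilot of BL33 against non-point needling is the natural source. Then restate the power, along these lines: *With 40 evaluable patients per group, a between-group difference of D points in 6-week IPSS change and an SD of S (both from the randomized pilot), the trial has P% power at a two-sided 5% level.*

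Add the 90%-power detectable difference over a range of SDs (about 2.1 points at 2.84, 2.9 at 4, 3.7 at 5), because the SD from a 40-patient pilot is itself uncertain. The 2.1 should not simply be adopted as the new target: it is back-calculated from the sample size and says nothing about which difference is expected or matters.

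The cost is one revised paragraph using data the sponsor already holds. The restated power may be less favourable than 90%, and whether 100 patients remain adequate should be judged from it.

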### Inclusion criteria

According to the diagnosis recommended by the fifth international BPH Consulting Committee, patients who meet the following criteria will be recruited: 1) 50-70 years old; 2) mild to moderate BPH evaluated by I-PSS; 3) patients having urinary dysfunction more than 3 months; 4) patients with stable life signs; 5) no use of α1 receptor blocker, 5α-reductase inhibitor or traditional Chinese medicine for over 1 week; 6) volunteer to join this research and give informed consent prior to receiving treatment.

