### Exclusion criteria

Patients with any of the following conditions will be excluded: 1) urinary dysfunction caused by gonorrhea or urinary tract infection; 2) oliguria and anuria caused by urinary calculi, prostate cancer, bladder tumor and acute/chronic renal failure; 3) urinary dysfunction caused by neurogenic bladder, bladder neck fibrotic and urethral stricture; 4) failure of invasive therapy for prostatic obstruction; 5) injured local organs, muscle and nerve caused by pelvic operation or trauma; 6) upper urinary obstruction and hydrocele combined with damaged renal function due to BPH diagnosed by B-ultrasound; 7) Patients unable to commit to treatment because of commuting problems to the hospital.

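### The eligibility lists admit men who have already had BL33 electroacupuncture, and such men may recognise their allocation in a trial that depends on patient blinding

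*Protocol article*

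**What the plan says.** All references are to the protocol article.

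- **Inclusion criteria.** Criterion 5 of six requires "no use of α1 receptor blocker, 5α-reductase inhibitor or traditional Chinese medicine for over 1 week". Acupuncture is not named.
- **Exclusion criteria.** There are seven entries. The one that concerns a treatment already tried is "failure of invasive therapy for prostatic obstruction"; none concerns acupuncture.
- **2.1 Design.** The washout appears again, for drugs only: "Patients on mediciation for urinary symptoms are requested to stop medication one week before baseline assessment". Then, "Before randomization, patients will complete 1-week baseline assessment".
- **Recruitment (2.1 Design).** The trial runs in a hospital acupuncture department, and "Participants are recruited from PBH clinic in the hospital by the use of local newspaper advertisements and posted notices at clinic site".
- **Background.** The team reports that "electroacupuncture at BL33 can reduce IPSS by 6.52 ± 0.41 (n = 47)[13] and 6.68 ± 2.84 (n = 87" in two cited reports, and describes a pilot in which 40 patients were randomised to BL33 or to a non-point beside it.
- **Interventions.** For the treatment group, needling into the S3 foramen is described as ending with sensation radiating to the perineum. The control site is 2 cun lateral, with the same manipulation and stimulation. The pilot is said to have shown the same feeling in both groups.
- **Discussion.** From the unseen site and the equal feeling the article concludes: "So patients are blinded as to which treatment they will receive". It attributes any difference between the groups entirely to point location.

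**The concern.** The trial asks whether needling at BL33 does more than identical needling a short distance away. Because everything except location is held equal, the answer depends on patients not knowing which site they receive. The primary outcome, IPSS reduction at week 6, is a symptom score that follows what the patient reports, so blinding the urologist who assesses it does not remove the effect of a patient's belief about his arm.

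A man who has had BL33 electroacupuncture brings a remembered sensation to compare with. The out-of-sight argument does not help there, because he would judge by feeling. If he recognises BL33 he may report more relief; if he notices its absence he may report less. Both push the arm difference towards BL33, and randomisation does not remove this, because the reaction arises after allocation and differs by arm.

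A second, weaker route is dilution: men who have already had the treatment may respond differently to a further course, which could narrow the contrast.

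The criteria admit these men, and the team has already treated patients at BL33.

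**Working it through.** **1. What gap is required?** Two readings of criterion 5 are possible.

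- Traditional Chinese medicine includes acupuncture: more than 1 week without it. With the drug rule's timing (stop one week before baseline, then a 1-week baseline assessment), this is about 1 + 1 = 2 weeks before needling.
- It means medicines only, as the wording in 2.1 Design suggests: no gap is required.

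For comparison, sessions end in week 4 and IPSS is assessed again in week 18, so the plan looks for an effect 18 − 4 = 14 weeks after treatment. This does not prove that an effect lasts so long, but it does show that a one-week gap is short by the plan's own horizon.

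**2. Does the blinding argument cover experienced men?** The pilot statement of equal feeling compares the two groups. It is not said to include men who had felt BL33 before, and perineal radiation is described only for BL33. The documents neither show nor rule out recognition by such men.

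**3. Size of a recognition bias.** No document gives the share of experienced men, f, or the shift, b, that recognition produces in their between-arm IPSS change. Both are assumed. With no true effect, bias = f × b.

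| f | b = 2 | b = 4 |
|---|---|---|
| 5% | 0.1 | 0.2 |
| 10% | 0.2 | 0.4 |
| 20% | 0.4 | 0.8 |
| 30% | 0.6 | 1.2 |

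**4. The standard deviation (SD).** The Patients section plans for a difference of 7 points, two-sided 5%, 90% power, and 50 per arm with 20% dropout. No planning SD is printed, so the sample size can be neither confirmed nor refuted. Back-solving with 50 × 0.8 = 40 evaluable per arm gives SD = 7 × √(40/2) / (1.960 + 1.282) = 9.66. The Background prints 2.84, read here as the SD of a within-group change. The standard error of the arm difference is SD × √(2/40): 2.16 for SD 9.66 and 0.635 for SD 2.84.

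**5. False-positive rate from recognition.** Type I error = Φ(bias/SE − 1.96) + Φ(−bias/SE − 1.96).

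| f | SD 9.66 | SD 2.84 |
|---|---|---|
| 10% (bias 0.2–0.4) | 5.1–5.4% | 6.1–9.7% |
| 20% (bias 0.4–0.8) | 5.4–6.6% | 9.7–24.3% |
| 30% (bias 0.6–1.2) | 5.9–8.6% | 15.7–47.2% |

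**6. Dilution.** Suppose a share f shows no BL33 versus non-point difference at all, which is an extreme assumption. The expected difference is 7 × (1 − f), and power = Φ(7(1 − f)/SE − 1.96). With SD 9.66:

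- f = 0: 90%
- f = 10%: difference 6.3, power 83.1%
- f = 20%: difference 5.6, power 73.7%
- f = 30%: difference 4.9, power 62.1%

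With SD 2.84, even f = 30% gives 4.9/0.635 = 7.7 standard errors, so power would hardly change. The loss therefore depends on the back-solved SD.

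**The case against.** **No one knows how many such men would enrol.** This stands. If the two earlier series do not overlap they hold 47 + 87 = 134 men, but the article does not say that they are separate or where they were run. Nor does it say how many of those men would still be eligible or would come back. A reader might infer from these counts that previously treated men will form a large part of the 100 enrolled; the documents do not support that.

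**Carry-over does not bias the comparison in one direction.** A reader might infer that residual benefit in previously treated controls shrinks the arm difference by some share of the 6.5-point reduction quoted in the Background. That does not follow. The outcome is change from baseline, so residual benefit is already in the baseline score. Randomisation spreads such men over both arms in expectation, and the 6.5 points is a within-group reduction, not an arm contrast. The Discussion itself expects control needling to achieve part of the effect. Only possible dilution is left.

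**The pilot found equal sensation.** This is fair evidence for patients in general, so one cannot say that blinding fails for experienced men. But the statement is not said to cover them.

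**The two routes oppose each other.** Recognition inflates the difference and dilution narrows it, and both may be small beside the planned 7 points. That is possible, but nothing in the plan shows that they cancel.

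**A journal article condenses.** A fuller protocol may screen for earlier acupuncture. The article nevertheless sets out its eligibility rules as complete, numbered lists, including a treatment washout, so the rule can be judged as stated.

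**Conclusion.** The concern holds as a risk of unknown size. The stated criteria let men with previous BL33 electroacupuncture enrol, including participants in the team's own earlier studies and pilot, after a gap of just over one week or none. Such men may recognise their allocation, and the pilot statement is not shown to answer this.

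Under an assumed 2 to 4 point shift, the bias is 0.2 to 0.4 IPSS points if 10% of men are experienced and 0.6 to 1.2 points if 30% are. It is small if few enrol. It matters most if the true arm difference is small or null, or if the SD is near 2.84. Dilution could lower power from 90% to 83% at a 10% share, but only under the back-solved SD and the assumption that these men show no arm difference.

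A reader might go further and conclude that the comparison is distorted. The documents do not show that: they give neither the share of such men nor any evidence that they recognise the needling. The point is worth acting on because the trial's claim rests on patient blinding and the remedy is cheap.

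**What to change.** Preferred: add an exclusion criterion for participation in the team's earlier BL33 studies or the pilot, and for previous acupuncture at BL33 or the adjacent sacral area, with a matching question at screening.

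At minimum: exclude the earlier study participants, record previous sacral acupuncture at baseline (site and date), and pre-state a sensitivity analysis of the primary outcome in men without it.

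In either case, state whether traditional Chinese medicine in inclusion criterion 5 covers acupuncture, and reconcile it with the drug-only wording in 2.1 Design.

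The cost is one eligibility line and one screening question, a few lost candidates and a slightly narrower population. Exposure that is not recorded at entry may not be reliably recoverable later.
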